## Abstract

**Background:**

Although results of case series support the use of spinal cord stimulation in failed back surgery syndrome patients with predominant low back pain, no confirmatory randomized controlled trial has been undertaken in this patient group to date. PROMISE is a multicenter, prospective, randomized, open-label, parallel-group study designed to compare the clinical effectiveness of spinal cord stimulation plus optimal medical management with optimal medical management alone in patients with failed back surgery syndrome and predominant low back pain.

**Method/Design:**

Patients will be recruited in approximately 30 centers across Canada, Europe, and the United States. Eligible patients with low back pain exceeding leg pain and an average Numeric Pain Rating Scale score ≥5 for low back pain will be randomized 1:1 to spinal cord stimulation plus optimal medical management or to optimal medical management alone. The investigators will tailor individual optimal medical management treatment plans to their patients. Excluded from study treatments are intrathecal drug delivery, peripheral nerve stimulation, back surgery related to the original back pain complaint, and experimental therapies. Patients randomized to the spinal cord stimulation group will undergo trial stimulation, and if they achieve adequate low back pain relief a neurostimulation system using the Specify® 5-6-5 multi-column lead (Medtronic Inc., Minneapolis, MN, USA) will be implanted to capture low back pain preferentially in these patients. Outcome assessment will occur at baseline (pre-randomization) and at 1, 3, 6, 9, 12, 18, and 24 months post randomization. After the 6-month visit, patients can change treatment to that received by the other randomized group. The primary outcome is the proportion of patients with ≥50% reduction in low back pain at the 6-month visit. Additional outcomes include changes in low back and leg pain, functional disability, health-related quality of life, return to work, healthcare utilization including medication usage, and patient satisfaction. Data on adverse events will be collected. The primary analysis will follow the intention-to-treat principle. Healthcare use data will be used to assess costs and long-term cost-effectiveness.

**Discussion:**

Recruitment began in January 2013 and will continue until 2016.

**Trial registration:**

Clinicaltrials.gov: NCT01697358 (http://www.clinicaltrials.gov)

## Background

Following lumbosacral spine surgery, between 5 and 50% of patients suffer from chronic back and/or leg pain, commonly known as failed back surgery syndrome (FBSS) [1,2] and characterized by disabling neuropathic radicular leg pain with or without low back pain, which might have mixed neuropathic and nociceptive pain components [3]. FBSS can be disabling and can have a negative impact on a patient’s health-related quality of life, well-being, and productivity [4,5].

Treatment of FBSS pain by further operations or medical management is often unsuccessful and places a heavy economic financial burden on healthcare systems [2,3]. In contrast, randomized controlled trials (RCTs) have shown spinal cord stimulation (SCS) to be a clinically effective and cost-effective adjunct to medical management [6-8] or alternative to a further operation [9,10] in patients with FBSS characterized by leg pain exceeding or equaling axial low back pain.

The effective targeting of the back pain component of FBSS remains a challenge [11-13]. Ongoing development of SCS leads and electrode arrays has included creation of an insulated paddle with a multicolumn design and a greater number of contacts than was formerly available: all of these features improve low back coverage [14-16]. A pilot study has demonstrated the efficacy of a multicolumn SCS lead configuration for the treatment of the axial back pain component of FBSS [17]. RCT evidence is needed to confirm the efficacy of the use of multicolumn SCS in patients with FBSS characterized by predominant back pain.

### Aims and objectives

The PROMISE study is a RCT comparing the clinical effectiveness of SCS using the Specify® 5-6-5 surgical lead (Medtronic, Inc., Minneapolis, MN, USA) plus optimal medical management (OMM) versus OMM alone in patients suffering from predominant low back pain due to FBSS. After the 6-month visit, patients can change treatment to that received by the other randomized group. All patients will be followed for 24 months post randomization.

The primary objective is to determine the difference in the proportion of patients receiving SCS plus OMM versus the proportion receiving OMM alone who have ≥50% reduction in back pain intensity, as measured by the Numeric Pain Rating Scale (NPRS), from baseline to 6 months. Secondary objectives are to compare changes in the following outcomes from baseline to 6 months between the two groups: low back pain intensity, as measured by the NPRS [18]; leg pain intensity, as measured by the NPRS [18]; functional disability, as measured by the Oswestry Disability Index [19]; and quality of life, as measured by the Short-Form Health Survey, version 2 physical component summary score [20]. Additional objectives include the comparison of other patient-related outcomes and healthcare utilization including medication usage (see below) at 6 months, to assess within-patient changes (that is, compared with pre-randomization) in outcomes from 6 to 24 months post randomization, to characterize all SCS-related and non-SCS-related adverse events, and to assess the costs and cost-effectiveness of SCS plus OMM versus OMM alone.

## Methods/Design

This protocol is reported in accord with the SPIRIT 2013 guidance for protocols of clinical trials [21].

### Design and setting

This multicenter study has an open-label, randomized, parallel-group design. Patients will be randomized 1:1 to SCS using the Specify® 5-6-5 surgical lead (Medtronic, Inc.) plus OMM (SCS group) or to OMM alone (OMM group) and followed for 6 months (Period I, randomized comparative phase). After completion of the 6-month (Period I) outcome assessment, patients will be systematically reminded (through electronic tablets used for questionnaire completion) that they have completed the randomized period of the study and can change treatment to that received by the other randomized group. Reasons for treatment switching will be recorded. Patients will be followed to 24 months post randomization (Period II, long-term observational follow-up phase).

The trial will be conducted at approximately 30 investigative sites globally, with approximately 15 to 20 sites in the USA and 10 to 15 sites in Europe and Canada. Additional locations may be added during the course of the study. No single center can exceed 10% of all randomized patients. The study design is summarized in Figure 1.

**Figure 1 F1:**
[figure not shown]
**PROMISE trial patient flow.** *Therapy change may occur at any time post 6-month visit. OMM, optimal medical management; SCS, spinal cord stimulation.

### Selection of patients

The study population comprises patients suffering from chronic low back (predominant) and leg pain due to FBSS. A patient must meet all of the inclusion criteria and none of the exclusion criteria to be eligible for the study.

#### **
*Inclusion criteria*
**

The subject is a candidate for SCS with the multicolumn Specify® 5-6-5 surgical lead (see Additional file 1); has FBSS and does not require further surgery (for the purposes of this study, FBSS is defined as persistent or recurrent low back and leg pain of at least 6 months duration, following at least one decompression and/or fusion procedure); presents average low back pain ≥5 and that is greater than leg pain as assessed by the baseline NPRS; and has persistent low back and leg pain despite other treatment modalities (pharmacological, surgical, physical, or psychological therapies) that have been tried and did not prove satisfactory, are unsuitable, or are contraindicated for the subject.

#### **
*Exclusion criteria*
**

The subject is being treated or has been treated with SCS, subcutaneous or peripheral nerve stimulation, being treated with an intrathecal drug delivery system or requires back surgery at the location related to his/her original back pain complaint or experimental therapies; had most recent back surgery less than 6 months ago; has low back pain only (no leg pain) as assessed by the baseline NPRS; is suspected by the investigator of substance abuse that might confound the study results; has unresolved major issues of secondary gain, as determined by the investigator; exhibits major psychiatric morbidity, untreated or refractory to treatment as determined by the investigator; has consistent severe pain (that is, 10 out of 10) without fluctuation, which might confound the results of this study; has radiographic evidence of instability requiring fusion; has pain relieved completely by recumbency (mechanical pain); has a serious neurologic deficit; has a history of coagulation disorder, lupus erythematosus, diabetic neuropathy, rheumatoid arthritis, or ankylosing spondylitis; has calcific arachnoiditis; has severe thoracic stenosis; has life expectancy < 24 months beyond study enrolment; is <18 years of age; is pregnant or planning to become pregnant during the course of the study; is enrolled in or plans to enroll in any study that might confound the results of this study; would be unable to operate the SCS equipment, based on the opinion of the principal or sub-investigator; is unwilling to be treated with SCS, attend visits as scheduled, and/or comply with study requirements; is unable to undergo study assessments or complete questionnaires independently (for example, is illiterate); and is a member of a vulnerable population.

A screening log will be kept at each site to identify potential subjects. All FBSS patients identified through standard clinical practice at the site (for example, call log, chart review, scheduled visits, and referrals) will be listed on the screening log. Potentially eligible subjects will be provided with detailed information about the study including a description of SCS and of OMM.

A patient is considered enrolled in the study upon completion of the informed consent process. Enrolled subjects will be taught how to complete a pain diary between the enrolment visit and the randomization visit. The subject will record his/her low back and leg pain scores during a 7-day pain diary period prior to randomization. Subjects will not be told what confirmatory pain scores are required for study inclusion. The inclusion criteria of average NPRS score to assess low back and leg pain will be evaluated after the subject completes the pain diary. Candidacy for SCS with the Specify® 5-6-5 implant will also be confirmed based on appropriate imaging according to usual practice. In addition, where a psychological evaluation (or other evaluation) is standard of care and/or required, the evaluation must take place prior to randomization. The principal investigator will document whether the patient has received the required evaluation and the results of that evaluation. FBSS diagnosis will also be confirmed based on appropriate imaging according to usual practice.

The principal investigator or his/her designee will review the diary to confirm that the pain intensity scores and pain location meet the inclusion/exclusion criteria (see above). In addition, the principal investigator will document that the patient is a candidate for implantation of a Specify® 5-6-5 SCS system. Upon confirmation of eligibility, OMM treatment planning and completion of the questionnaires, subjects will be randomized to one of the two treatment groups. Subjects who do not complete or meet preliminary eligibility requirements will not be randomized and will be exited from the study.

### Interventions

Pain treatment will be evaluated, and medical management of patient’s pain will be optimized in both arms. As part of the confirmation of eligibility (prior to randomization), the investigator and subject will determine an individual OMM treatment plan, which should include non-investigational pharmacologic agents (for example, tricyclic antidepressants, opioid analgesics or tramadol, antiepileptics, or lidocaine) and/or interventional therapies (for example, therapeutic injections, radiofrequency, acupuncture, functional restoration, physical therapy, and psychological interventions, such as cognitive behavioral therapy) as appropriate. The following treatments are excluded from OMM: intrathecal drug delivery, peripheral nerve stimulation (not an approved indication in the United States), back surgery at the location related to the patient’s original back pain complaint, and experimental therapies. Data regarding pain treatments implemented during the study will be collected to reveal how medical management was optimized. After randomization, as well as at all scheduled follow-up visits, the subject and physician will further discuss OMM to determine the best course of continued action.

In addition to OMM, patients randomized to the SCS arm will undergo an SCS screening test (3-day minimum). The screening test may be conducted with the Specify® 5-6-5 surgical lead or with a percutaneous lead(s). If successful, a SCS system will be implanted. A screening test will be determined to be successful if the subject finds the feeling of paresthesia acceptable and has adequate low back pain relief with usual activity and appropriate analgesia as assessed by the physician. Physicians can consider a conducting second screening test with the Specify® 5-6-5 lead if a screening test with a percutaneous lead led to inadequate paresthesia coverage of low back pain and/or painful extraneous stimulation (for example, chest wall pain, pressure or sharp mid-back pain). The final system implanted will consist of a Medtronic pulse generator (rechargeable or primary cell) and a Specify® 5-6-5 surgical lead. Subjects should receive their permanent implant within 60 calendar days from randomization. They will be programmed to their optimal programming parameters and will be able to adjust their stimulation with the patient programmer, within the settings programmed in the clinic. Subjects will be provided with a patient programmer manual and will be instructed on the proper use and handling of the patient programmer. Subjects who fail the screening test (and do not proceed to implant) will be followed in the study according to the principles of intention-to-treat analysis.

### Assessments

Outcome measures selected for this trial are based on a review of the previous RCTs of SCS and a consideration of IMMPACT recommendations [18].

The day of randomization is day 0 for the study periods. Subjects will be assessed prior to randomization (baseline) and at 1-month, 3-month, 6-month, 9-month, 12-month, 18-month and 24-month follow-up visits. Visit windows for Period I and Period II will remain constant based on the original date from the randomization visit, regardless of whether any change in therapy occurs. Assessments will be performed by appropriately trained and delegated study staff according to the usual practices of the site. Electronic case report forms will be used for this study with patients completing the study questionnaires confidentially on electronic tablets, and these data will be uploaded to a web-based server. Table 1 provides a summary of the data collection process and timing.

**Table 1 T1:** PROMISE study – summary of data collection

**Study procedure**	**Enrollment**	**Randomization**	**Screening test**	**Implant**	**1 month**^ **a** ^	**3 months**^ **b** ^	**6 months**^ **b** ^	**9 months**^ **b** ^	**12 months**^ **b** ^	**18 months**^ **b** ^	**24 months**^ **b** ^	**Unscheduled**	**Early discontinue**^ **c** ^
Time window (days)	-90 to 0	0	0 to 57	3 to 60	10 to 67	68 to 137	138 to 228	229 to 319	320 to 455	456 to 637	638 to 789	NA	NA
Informed consent	**X**												
Demographics (age, gender)	**X**												
Medical history	**X**												
Inclusion/exclusion criteria	**X**	**X**											
Pain location	**X**	**X**											
Pain diary (complete prior to visit)		**X**			**X**	**X**	**X**	**X**	**X**	**X**	**X**		**X**
OMM treatment plan		**X**			**X**	**X**	**X**	**X**	**X**	**X**	**X**		
Questionnaires (ODI, SF-36, EQ-5D^d^, Pittsburgh Sleep Quality Index, employment status, pain and/or paresthesia map)		**X**				**X**	**X**	**X**	**X**	**X**	**X**		**X**
Randomization assignment		**X**											
Neuropathic pain (DN4)		**X**											
PGIC, Patient satisfaction with therapy						**X**	**X**	**X**	**X**	**X**	**X**		**X**
Nondrug pain treatment and other healthcare use assessment		**X**	**X**	**X**	**X**	**X**	**X**	**X**	**X**	**X**	**X**		**X**
Payer information (US only)	**X**								**X**		**X**		
Medication assessment		**X**	**X**	**X**	**X**	**X**	**X**	**X**	**X**	**X**	**X**		**X**
Event assessment^d^		**X**	**X**	**X**	**X**	**X**	**X**	**X**	**X**	**X**	**X**	**X**	**X**
Screening test assessment			**X**										
Implant information			**X**	**X**									
Request for change in randomized therapy							**X**	**X**	**X**	**X**	**X**	**X**^ **e** ^	
SCS therapy thresholds							**X**						
Device interrogation (initial and final)				**X**^ **f** ^	**X**	**X**	**X**	**X**	**X**	**X**	**X**	**X**	**X**

DN4, Douleur neuropathique en 4 questions; ODI, Oswestry Disability Index; OMM, optimal medical management; PGIC, Patient Global Impression of Change; SF-36, Short-Form 36; SCS, spinal cord stimulation.

^a^For subjects randomized to SCS, the 1-month visit should occur a minimum of 7 days after implant (or screening test if the test was unsuccessful).

^**b**^Visits should occur within the window but at least 2 weeks after the previous visit.

^c^Early discontinuation, collect data if possible.

^d^When possible, collect additional EuroQoL (EQ-5D) at time of event if device-related event requiring surgical intervention or hospitalization occurred.

^e^Only after 6 months.

^f^No initial interrogation at implant, final only.

#### **
*Primary outcome*
**

The primary outcome is the proportion of subjects with ≥50% reduction in low back pain intensity measured using the NPRS at 6 months [18]. Pain relief will be assessed as a reduction of the 11-point NPRS. Patients will record their low back and leg pain using a (paper) pain diary two times per day, once in the morning and once in the evening, for a 7-day period within 2 weeks prior to the randomization visit and subsequent scheduled study visits. For the initial baseline pain diary, patients are required to complete at least 5 of 7 days in their entirety, or they will not proceed to randomization. The proportion of subjects in each group with ≥50% reduction in average low back pain score at the end of Period I compared with baseline will be calculated.

#### **
*Secondary outcomes*
**

Secondary outcomes are: Back and leg NPRS score [18]; Oswestry Disability Index version 2 [19]; and Physical Component Summary score on the Short-Form 36 [20].

Other outcomes include: Mental Component Summary score on Short-Form 36 [20]; EuroQoL 5D-5 L (EQ-5D-5 L) [22]; Pittsburgh Sleep Quality Index [23]; healthcare use related to the pain condition and to its treatment (for example, managing adverse events, interventions, investigations, drugs, length and number of inpatient hospitalizations, and number of emergency room, office, and other healthcare-related visits) [24]; employment status ('What is your current employment status?’ , 'If out of work: what is the main reason you are out of work?’); patient satisfaction ('Would you recommend this therapy to patients suffering from pain similar to yours?’ , 'Overall how satisfied or unsatisfied are you with this therapy?’); Patient Global Impression of Change version 2 [25]; programming parameters and paresthesia coverage; and adverse events (adverse events and device deficiencies documentation will include date of adverse event or device deficiency, diagnosis and description of the event, assessment of seriousness of the event, treatment of the event, outcome or resolution and date of the event, and relationship of the event to the device or to OMM – in addition to the standard questionnaire data collection schedule, the EQ-5D-5 L will be collected, when possible, whenever a device-related adverse event occurs that might require a surgical intervention or hospitalization).

#### **
*Process measures*
**

At the screening and baseline visits, the following additional information will be collected: subject demographics (for example, age, gender) and a neuropathic pain assessment by clinician-administered diagnostic questionnaire (Douleur Neuropathique en 4 questions) to discriminate neuropathic pain components of low back pain [26]. Subjects who proceed to device implantation will have the following information collected: pain/paresthesia map, parameter settings, electrode location, and device implant information (that is, model, serial number). Patients receiving SCS therapy will have a device interrogation at each visit, and at only the 6-month visit data will be gathered on the parameters at which SCS paresthesia is perceived, is comfortable, and becomes uncomfortable. Unscheduled patient visits could occur between scheduled study follow-up visits due to patient discontinuation from the study or device reprogramming and management of any complications.

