Missing data are a potential source of bias. A rigorous study design and execution will help prevent the incidence of missing data from occurring. For the primary objective, patients with missing data at the end of Period I will be treated as nonresponders (failures). With this approach, we assume that nonresponders in both treatment groups have no change in their outcomes compared with baseline. This method has been chosen over more complex imputation methods, such as multiple imputation, because it has been empirically demonstrated in trials of chronic pain to produce conservative treatment effects [28]. For the secondary study objectives, no change from baseline will be assumed for patients with missing data. For completers’ and as-treated supporting analyses, only completers will be included in the analysis.

Period II is the long-term follow-up phase, which includes the possibility for patients to change from their original treatment assignment to the alternative treatment. The objectives of Period II are to compare within-patient changes (that is, baseline versus follow-up) in each group. Because the study design allows patients to change from the randomized treatment group to the alternative treatment after 6 months of follow-up, the analysis of objectives in Period II will be based on the treatment patients actually received and not on the randomization assignment. Only completers will be included.

Unadjusted *P* values will be reported. To maintain an overall type I error rate at 0.05, a fixed-sequence method for the multiplicity adjustment of hierarchical endpoints will be used to test the primary and secondary objectives. No multiplicity adjustment will be performed for evaluations of the additional study objectives. A validated statistical software package will be used for the analyses of the study results (for example, SAS, SPLUS). These analyses are detailed in a statistical analysis plan.

#### **
*Economic evaluation*
**

Economic analyses consider the costs and effectiveness of treatments. Costs will be calculated by multiplying units of healthcare use used by the cost of each unit. Effectiveness will be expressed as quality-adjusted life-years, with these data derived from patients’ responses to the EQ-5D-5 L.

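### Period II groups patients by treatment received but measures change from before randomization, so a switcher's result mixes pre-switch change with change under the new treatment

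*Protocol article*

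**What the plan says.** Four statements in the protocol article bear on this point.

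- **Reference value.** Aims and objectives lists, among the additional objectives, "to assess within-patient changes (that is, compared with pre-randomization) in outcomes from 6 to 24 months post randomization". Data analysis repeats it: "The objectives of Period II are to compare within-patient changes (that is, baseline versus follow-up) in each group". Assessments defines baseline as the assessment before randomization.
- **Grouping.** Data analysis says that "the analysis of objectives in Period II will be based on the treatment patients actually received and not on the randomization assignment", in completers only.
- **Calendar.** Under Assessments, "The day of randomization is day 0 for the study periods", and the visit windows of both periods "will remain constant based on the original date from the randomization visit, regardless of whether any change in therapy occurs".
- **Switching.** Design and setting, with the note to Figure 1, allows a change to the other arm's treatment at any time after the 6-month visit. In Table 1 the row "Request for change in randomized therapy" is ticked at each scheduled visit from month 6 and, after month 6, at unscheduled visits. The unscheduled column has no tick for the pain diary or the questionnaires.

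The article gives switchers no second reference value, no time scale counted from the change, and no separate stratum.

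**The concern.** Each rule is reasonable alone, but together they describe something other than change under the treatment that names the group. An OMM patient who switches to SCS brings a baseline that predates the whole OMM-only period. During that period OMM is being actively optimized (Interventions), and entry required an average low back pain score of at least 5, so some change before SCS is plausible. That change becomes part of the figure reported under SCS. The same holds in reverse for a patient who leaves SCS for OMM.

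Time has a parallel problem. A month-12 value means 12 months since randomization, and for a switcher it may mean a few months of stimulation or less. The protocol attends to time since implant in one place: a footnote to Table 1 requires a minimum interval between implant and the 1-month visit for patients randomized to SCS. Switchers have no equivalent.

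At stake is how the long-term results can be read. A Period II curve by treatment received could be taken as effect by duration of SCS, which these rules do not deliver.

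**Working it through.** The plan gives no figure to reproduce, so this is calendar arithmetic on its own days.

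**Inputs from the article**
- Implant for patients randomized to SCS: day 3 to 60 (Table 1; Interventions gives the 60-day limit).
- 6-month window: day 138 to 228, midpoint (138 + 228)/2 = 183.
- 12-month window: day 320 to 455, nominal day 365.
- 18-month visit: nominal day 548.

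**Assumptions**
- The switch is made at the 6-month visit.
- The implant follows 3 to 60 days later. The article gives no interval for switchers.
- One month is 365.25/12 = 30.44 days.

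**1. Time on OMM before any SCS.** The earliest 6-month visit is day 138 and baseline precedes day 0, so the reference value is at least 138 days (138/30.44 = 4.5 months) older than the switch.

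**2. SCS exposure at month 12** (visit day minus implant day)

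| | Nominal visit days | Window limits |
|---|---|---|
| Randomized to SCS | 365 − 60 = 305 to 365 − 3 = 362 days (10.0 to 11.9 months) | 320 − 60 = 260 to 455 − 3 = 452 days (8.5 to 14.9 months) |
| Switched at the 6-month visit | 365 − 183 − 60 = 122 to 365 − 183 − 3 = 179 days (4.0 to 5.9 months) | 320 − 228 − 60 = 32 to 455 − 138 − 3 = 314 days (1.1 to 10.3 months) |

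A later switch brings exposure towards zero. For the month-6 switcher, the 18-month visit (548 − 183 − 60 = 305 to 548 − 183 − 3 = 362 days) matches the randomized SCS patient's month 12.

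**3. Effect of the reference value** (illustrative pain scores: baseline, month 6 on OMM, month 12 on SCS)

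| Scores | Reduction from pre-randomization | Reduction from pre-switch value |
|---|---|---|
| 8, 6, 4 | (8 − 4)/8 = 50% | (6 − 4)/6 = 33% |
| 8, 8, 4 | 50% | (8 − 4)/8 = 50% |
| 8, 9, 4.2 | (8 − 4.2)/8 = 47.5% | (9 − 4.2)/9 = 53.3% |

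Improvement on OMM enlarges the change shown under SCS, worsening shrinks it, and no change leaves it alone.

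**4. Share affected, if switchers are pooled.** The switch rate is not given. With equal arms, every patient in the SCS arm implanted and a fraction s of the OMM arm switching at month 6, switchers are s/(1 + s) of the SCS group. For s = 10%, 50% and 90% this is 9%, 33% and 47%. Taking the 60-day implant in both groups (10.0 and 4.0 months), mean exposure at month 12 falls from 10.0 to 9.5, 8.0 and 7.2 months.

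**5. Age of the last pre-switch value.** If a change is requested at an unscheduled visit shortly before month 18, the last diary may date from month 12: 548 − 365 = 183 days, about 6 months.

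**The case against.** The other side has several good points.

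- **Pooling is not spelled out.** A reader might infer that the protocol merges switchers with randomized SCS patients. That is the natural reading, but reporting by treatment sequence would also fit the wording, and the statistical analysis plan, which is not shown, could do so. This stands. Separating switchers would deal with the mixed exposure, but not with the reference value, which the article fixes.
- **The calendar is not an error.** A reader might take the constant visit windows as a faulty analysis clock. The sentence sets scheduling, and the economic evaluation needs the randomization calendar at 6, 12 and 24 months.
- **The direction is open.** A reader might infer that the rule favours SCS. The third example in the working runs the other way.
- **Switchers are not misclassified as responders.** The 50% threshold is defined for the end of Period I, and no responder rule is stated for Period II. The percentages in the working only illustrate the effect of the reference.
- **Change from pre-randomization is a legitimate description.** SCS is given on top of OMM, so patients randomized to SCS also carry OMM optimization and regression to the mean. A common reference describes everyone's whole course, and it should be kept.
- **A pre-switch reference has its own bias.** If patients ask to switch when pain is high, the later value will tend to fall back. That argues for showing both references rather than replacing one with the other.
- **The article promises no effect by duration of SCS**, and calls Period II observational. This limits the weight of the point but does not make the switchers' figures readable.

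**Conclusion.** The point holds in a limited form. As written, a switcher's Period II change is measured from a value at least 138 days before the switch, is grouped by treatment received, and carries a visit label that is not time on that treatment. At nominal month 12 the gap in SCS exposure is about 4 to 6 months against about 10 to 12 months.

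The 138 days and the exposure of randomized SCS patients follow from Table 1 and nominal visit days. The switchers' exposure rests on a switch at month 6 and an implant 3 to 60 days later. The share affected depends on an unknown switch rate and on pooling, which is inferred. The size and sign of the effect on pain change depend on how switchers fared before switching, and the effect is nil if they did not change.

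The randomized 6-month primary and secondary comparisons are untouched. This is a matter of making the observational phase interpretable, and it does not threaten the trial's main conclusion.

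**What to change.** 1. In Aims and objectives and in the Period II paragraph of Data analysis, state that results are shown by treatment sequence (stayed on SCS, stayed on OMM, OMM to SCS, SCS to OMM) rather than pooled by current treatment.
2. For switchers, report change from the last diary and questionnaires before the switch, by time since implant or since the change, alongside change from pre-randomization. Note that the pre-switch value may carry regression to the mean if patients switch when pain is high.
3. In Table 1, where a change is requested at an unscheduled visit, add the 7-day diary and the tablet questionnaires before the change. Analysis cannot recover this value later.
4. Leave the visit calendar in Assessments unchanged.

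Items 1 and 2 are wording. The diaries at scheduled visits, the implant information and the record of SCS being added or removed are already collected. Item 3 adds one data set per switch requested between visits. The price is smaller Period II groups with less precise estimates, and a small added burden on those patients and sites.
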